**Table 5. Immunization Plan**

| Group     | Number
Of
Subjects | Week            |                    |                        |                    |                        |                    |                |                        |                      |
|------------------|-----------------------------------|------------------------|--------------------|------------------------|--------------------|------------------------|--------------------|----------------|------------------------|----------------------|
|                  |                                   | 0               | 2           | 4               | 6           | 8               | 10          | 12      | 14              | ~38           |
| DNA-L+rTV | 12                         | DNA
2mg     |                    | DNA
2mg     |                    | DNA
2mg     |                    | rTV     |                        | Follow
up |
| DNA-H+rTV | 12                         |                        | DNA
4mg |                        | DNA
4mg |                        | DNA
4mg |                | rTV             | Follow
up |
| DNA       | 6                          |                        | DNA
4mg |                        | DNA
4mg |                        | DNA
4mg |                | rTV
placebo | Follow
up |
| placebo   | 6                          | DNA
placebo |                    | DNA
placebo |                    | DNA
placebo |                    | placebo |                        | Follow
up |

Note:

(1) DNA vaccine is composed of 1/2 pGP140 and 1/2 pGPNef. Each of the two plasmids was collected by 1ml for intramuscular injection at the bilateral deltoids of upper arms.

Control group: The placebo 1ml was collected for intramuscular injection at the bilateral deltoids of upper arms.

(2) The rTV vaccine was vaccinated for 2 poxes using a bifurcated needle on one side of the upper arm, and two bifurcated needles of placebo were vaccinated in the placebo group.

Table 6. Follow-up plan (the vaccination week is week 0)

| Weeks                                                | -2 | 0   | 1 | 2 | 4   | 5 | 6 | 8   | 9 | 10 | 12  | 12.5           | 13 | 14 | 16 | 20 | 24 | 28 | 32 | 36             |
|------------------------------------------------------|----|-----|---|---|-----|---|---|-----|---|----|-----|----------------|----|----|----|----|----|----|----|----------------|
| Vaccination                                          |    | DNA |   |   | DNA |   |   | DNA |   |    | rTV |                |    |    |    |    |    |    |    |                |
| Personal information collection /HIV test counseling | X  |     |   |   | X   |   |   | X   |   |    | X   |                |    | X  | X  | X  | X  | X  | X  | X              |
| Physical Examination                                 | X  | X   | X | X | X   | X | X | X   | X | X  | X   | X              | X  | X  | X  | X  | X  | X  | X  | X              |
| Anterior-posterior chest X-ray                       | X  |     |   |   |     |   |   |     |   |    |     |                |    |    |    |    |    |    |    | X              |
| Electrocardiogram a                                  | X  |     |   |   | X   |   |   | X   |   |    | X   |                | X  | X  | X  | X  | X  | X  | X  | X              |
| Routine blood test                                   | X  |     |   |   | X   |   |   | X   |   |    | X   |                | X  | X  | X  | X  | X  | X  | X  | X              |
| Routine urine test                                   | X  |     |   |   | X   |   |   | X   |   |    | X   |                | X  | X  | X  | X  | X  | X  | X  | X              |
| Liver and kidney functions and CK                    | X  |     |   |   | X   |   |   | X   |   |    | X   | X b | X  | X  | X  | X  | X  | X  | X  | X              |
| CK-MB and cTnI a                                     | X  |     |   |   | X   |   |   | X   |   |    | X   | X              | X  | X  | X  | X  | —  | —  | —  | X              |
| HIV antibody                                         | X  |     |   |   | X   |   |   | X   |   |    | X   |                |    | X  | X  | X  | X  | X  | X  | X              |
| HIV nucleic acid c                                   | X  |     |   |   |     |   |   |     |   |    |     |                |    |    |    |    |    |    |    | X              |
| HBsAg and HCV antibody                               | X  |     |   |   |     |   |   |     |   |    |     |                |    |    |    |    |    |    |    | X              |
| Syphilis test                                        | X  |     |   |   |     |   |   |     |   |    |     |                |    |    |    |    |    |    |    | X              |
| Urine pregnancy                                      | X  | X   |   |   | X   |   |   | X   |   |    | X   |                |    |    |    | X  | X  | X  | X  | X              |
| DNA/ANA antibody                                     | X  |     |   |   | X   |   |   | X   |   |    | X   |                |    |    |    |    |    |    |    | X              |
| Immune function                                      | X  |     |   |   |     |   |   |     |   |    | X   |                |    |    |    |    |    |    |    | X e |
| HLA typing                                           |    | X   |   |   |     |   |   |     |   |    |     |                |    |    |    |    |    |    |    |                |
| HIV antigen specific antibody (ELISA) d              |    | X   |   |   | X   |   | X | X   |   | X  | X   |                |    | X  | X  | X  | X  | X  | X  | X              |
| HIV cellular immune response (ELISPOT)               |    | X   |   |   | X   |   | X | X   |   | X  | X   |                |    | X  | X  | X  | X  | X  | X  | X              |
| HIV intracellular staining (ICS)                     |    | X   |   |   | X   |   | X | X   |   | X  | X   |                |    | X  | X  | X  | X  | X  | X  | X              |
| HIV neutralizing antibody d                          |    | X   |   |   | X   |   | X | X   |   | X  | X   |                |    | X  | X  | X  | X  | X  | X  | X              |

|                                 |   |  |  |  |  |  |  |  |  |   |   |   |   |   |   |   |   |   |   |
|---------------------------------|---|--|--|--|--|--|--|--|--|---|---|---|---|---|---|---|---|---|---|
| Vaccinia antibody        | X |  |  |  |  |  |  |  |  | X |   |   | X | X | X | X | X | X | X |
| Vaccinia viremia testing |   |  |  |  |  |  |  |  |  |   | X | X | X | X |   |   |   |   |   |

Notes:

- a: If total creatine kinase (CK) levels are abnormal, additional tests for CK-MB, cardiac troponin, and electrocardiogram (ECG) should be performed at increased frequency, with repeated testing in the short term. The timing of these tests will be determined by the clinical physician.
- b: Only CK testing is required.
- c: If HIV antibody testing is positive after vaccination, HIV nucleic acid testing should also be performed.
- d: Collect specimens at the corresponding time points for centralized antibody testing.
- e: Only immunoglobulin G, A, and M levels will be tested during this follow-up visit.

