The Ib phase requires 36 subjects, including those who have and have not been vaccinated against smallpox, with a study duration of 38 weeks. The primary objective is to observe the safety and tolerability of a combined immunization regimen involving three doses of either 2 mg or 4 mg of the DNA vaccine and one dose of the rTV vaccine in healthy volunteers, and to preliminarily assess its immunogenicity. Subjects will be divided into a combined immunization group, a DNA-only immunization group, and a placebo group. The first two groups will receive three doses of either 2 mg or 4 mg of the DNA vaccine at four-week intervals. Four weeks after the last DNA vaccine administration, the combined immunization group will receive the rTV vaccine at a dose determined in the Ia phase trial, while the DNA-only group will receive a corresponding dose of the rTV vaccine placebo; the placebo group will receive the same volume of solvent for the DNA or rTV vaccine at the same time points. After each vaccination, subjects will be closely monitored for systemic and local reactions, and safety and HIV antigen-specific immune responses will be observed for at least 24 weeks following the rTV vaccine (or placebo) administration.

Following the approval of the Phase Ia clinical trial protocol by the Ethics Review Committee

of the National Clinical Trial Base at Peking Union Medical College Hospital and the Ethics Review Committee of the Center for Disease Control and Prevention of Sexually Transmitted Diseases and AIDS in China, the Phase Ia clinical trial was officially initiated at Peking Union Medical College Hospital and conducted in strict accordance with the Good Clinical Practice (GCP) guidelines, ensuring the protection of the subjects' interests while adhering to the research protocol.

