## **2.4 Product Package, Doses and Method of Vaccination**

DNA vaccine is a colorless transparent liquid. It is supplied in 2ml vials with each vial of 2.0mg/1ml. The package specifies HIV-1 DNA vaccine (pGPNEF) or HIV-1 DNA vaccine (pGP140) and is stored at -70 °C. Each of the two plasmids was collected by 1ml for

intramuscular injection at the bilateral deltoids of upper arms.

The rTV vaccine is a pale yellow or light brown turbid and viscous liquid. It is supplied in 0.4ml/vial. The package indicates recombinant vaccinia virus (rTV) AIDS vaccine and is stored at -20 °C. The vaccination is performed with skin pricking method using a bifurcated needle. The vaccination method is as follows: insert the bifurcated needle into the vaccine vial, making it stained with enough vaccine liquid. Position your wrist against the vaccinated upper arm, perpendicularly direct the bifurcated needle to an area of 5mm in diameter at the deltoid of upper arm, and quickly prick 15 times. Prick with strength to the extent that bleeding points should appear at the pricking site in 15 to 30 seconds. If second smallpox will be vaccinated in the ipsilateral arm, another needle is needed to stain with vaccine for another vaccination at a site 2 cm away from the first vaccination site. When the site of vaccination becomes a little dry, it will be covered with gauze and dry breathable film.

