dose subgroup. Enrollment and vaccination will begin with the low-dose subgroup of the combined immunization group in the order of enrollment. The safety of the vaccine will be assessed within two weeks after each DNA vaccination in the low-dose subgroup. If no more than two vaccine-related adverse events of grade  $\geq 3$  (excluding fever above 39°C for no more than 3 days) occur, the trial will continue; if three or more such adverse events occur, subsequent vaccinations will be halted. Participants in both dose subgroups of the combined immunization group and the DNA-only group will receive three doses of 2 mg (low-dose subgroup) or 4 mg (high-dose subgroup) of the DNA vaccine at 4-week intervals. Enrollment and vaccination for the DNA-only group will commence simultaneously with the high-dose subgroup of the combined immunization group. If no more than two vaccine-related adverse events of grade  $\geq 3$  occur after each 4 mg DNA vaccination in the high-dose subgroup and the DNA-only group, the trial will continue; if three or more such adverse events occur, subsequent vaccinations in that dose subgroup will be stopped. If no more than two vaccine-related adverse events of grade  $\geq 3$  occur after the third DNA vaccination in each group, the combined immunization group will receive the rTV vaccine at the dose determined by the Phase Ia trial four weeks after the last DNA vaccination, while the DNA-only group will receive a placebo of the corresponding dose of the rTV vaccine. The placebo group will begin enrollment and vaccination at the same time as the low-dose subgroup of the combined immunization group and will receive placebos of the same volume as the DNA or rTV vaccines at the same time points. After the last vaccine or placebo administration, all participants will undergo at least six consecutive months of clinical and laboratory observation. In the Phase Ib trial, the interval between vaccinations in each group will be  $\geq 4$  weeks; if the time required for adverse reactions to heal or resolve exceeds 4 weeks, the interval between vaccinations will be  $\geq$  the actual time required for healing. The criteria for determining adverse events and their relationship to vaccination are detailed in Appendix 2 and Table 9.

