### **6.10.3 Randomization**

To avoid subjective selection bias by researchers and severe imbalance in sample allocation, a block randomization method will be employed in this trial. The random number table for randomization will be generated by statisticians from the Health Statistics Office of the Chinese Center for Disease Control and Prevention using SAS 9.1.2 software.

The 36 participants will be divided into two phases based on the order of enrollment, with 18 participants in each phase. In the first phase, participants will be randomized in a 2:1 ratio to either the low-dose combined immunization group or the placebo group. In the second phase, participants will be randomized in a 2:1 ratio to either the high-dose combined immunization group or the DNA-only group.

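### The single DNA preparation instruction delivers 4 mg, twice the 2 mg assigned to the low-dose arm, and the placebo volume is ambiguous

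*Protocol*

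**What the plan says.** Section 2.4 of the protocol describes two plasmids packed in separate vials and gives their strength: "It is supplied in 2ml vials with each vial of 2.0mg/1ml". It then gives the volume to draw, and Note (1) under Table 5 repeats the instruction: "Each of the two plasmids was collected by 1ml for intramuscular injection at the bilateral deltoids of upper arms". Neither place ties that volume to a dose level or an arm. Note (1) also fixes the composition as half of each plasmid: "DNA vaccine is composed of 1/2 pGP140 and 1/2" pGPNef.

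Section 6.4.2 assigns "three doses of 2 mg (low-dose subgroup) or 4 mg (high-dose subgroup) of the DNA vaccine at 4-week intervals". Table 5 prints 2 mg for DNA-L+rTV at each of its three DNA vaccinations, and 4 mg for DNA-H+rTV and for the DNA-only arm.

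For placebo, the same note says "The placebo 1ml was collected for intramuscular injection at the bilateral deltoids of upper arms". Section 6.4.2 states that the placebo group "will receive placebos of the same volume as the DNA or rTV vaccines at the same time points", and the Synopsis has the same rule: "the placebo group will receive the same volume of solvent for the DNA or rTV vaccine at the same time points". Section 6.10.3 sets which arm placebo is randomised against: "In the first phase, participants will be randomized in a 2:1 ratio to either the low-dose combined immunization group or the placebo group".

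**The concern.** One volume at one strength cannot produce two different doses, yet the protocol gives a single volume and strength for arms assigned 2 mg and 4 mg. The volume suits the high dose, and the arm for which it is wrong is the one that starts first.

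If the note were followed as written:

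- The low-dose arm would receive the high dose from the first vaccination. The safety assessment meant to come before 4 mg is given would itself be made at 4 mg, and the rule in section 6.7.2 that stops vaccination in all groups on low-dose events would run on 4 mg data.
- The 2 mg part of the primary safety objectives in section 6.1 would have no data. Those objectives observe each dose and do not compare them, so the loss would be one of information, not of power.
- The high-versus-low dose term in the immunogenicity model of section 6.10.5, and the corresponding question in Table 3, would compare two arms given the same dose.

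The placebo wording adds a smaller problem. Placebo is the blinded comparator of the low-dose arm. Equal injected volume is required, but neither volume is stated clearly.

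**Working it through.** **Inputs**

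- Strength: 2.0 mg/ml for each plasmid (section 2.4). Annex 4 gives a release range of 1.8 to 2.2 mg/ml and a labelled fill of 1.0 ml per vial.
- Volume drawn: 1 ml of each of two plasmids (section 2.4 and Table 5, Note (1)).
- Composition: half of each plasmid (Note (1)).
- Assigned doses: 2 mg for DNA-L+rTV; 4 mg for DNA-H+rTV and DNA-only (section 6.4.2, Table 5).
- Vaccinations: 3 DNA doses per participant; 12 participants in DNA-L+rTV.

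**Dose from the written instruction**

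Dose = plasmids x volume per plasmid x strength

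- Nominal: 2 x 1.0 ml x 2.0 mg/ml = 4.0 mg.
- Over the release range: 2 x 1.0 x 1.8 = 3.6 mg to 2 x 1.0 x 2.2 = 4.4 mg.

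This reproduces the 4 mg of the two high-dose arms. It does not reproduce the 2 mg of DNA-L+rTV, which lies below even the lower end of the range.

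- Per participant over three doses: 3 x 4.0 = 12.0 mg (10.8 to 13.2 mg) against 3 x 2 = 6 mg assigned.
- Administrations covered: 12 x 3 = 36.
- High-to-low dose ratio: 4/4 = 1.0 by the note; 4/2 = 2.0 as assigned.

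**Other readings of the instruction**

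| Reading | Dose delivered | Fits 2 mg arm | Fits 4 mg arms |
|---|---|---|---|
| 1 ml of each plasmid (as written) | 4.0 mg | no | yes |
| 1 ml in total of the half-and-half mix | 2.0 mg | yes | no |
| Dose label means mg per plasmid | 2.0 mg of each | yes | no (needs 2 ml of each) |
| 1 ml of each plasmid on each side | 8.0 mg | no | no |

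No reading serves both dose levels. The second conflicts with the statement that 1 ml is taken of each plasmid. The third conflicts with a dose made up of half of each.

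**Volume that 2 mg needs**

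Volume per plasmid = (dose / 2) / strength

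- 2 mg: (2 / 2) / 2.0 = 0.5 ml of each, 1.0 ml in total.
- 4 mg: (4 / 2) / 2.0 = 1.0 ml of each, 2.0 ml in total.
- Alternative for 2 mg by dilution to 1.0 mg/ml: 2 x 1.0 ml x 1.0 mg/ml = 2.0 mg, 2.0 ml in total.

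**Placebo volume against low-dose volume (totals)**

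| Low-dose preparation | Placebo 1 ml in total | Placebo 1 ml per side |
|---|---|---|
| 0.5 ml of each plasmid (1.0 ml) | 1.0 vs 1.0: match | 1.0 vs 2.0: differ |
| 1 ml of each plasmid (2.0 ml) | 2.0 vs 1.0: differ | 2.0 vs 2.0: match |

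Two of the four combinations match and two differ two-fold. The second row applies both to the undiluted draw in the note and to the diluted alternative.

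**The case against.** The strongest reply is that the note is incomplete and not miscalculated. It is correct for 18 of the 30 participants who receive DNA, and it sits directly under a table that prints 2 mg three times for the low-dose arm. Anyone told to give 2 mg, half of each plasmid, from 2.0 mg/ml vials can work out 0.5 ml plus 0.5 ml. The sponsor supplies instructions for use (section 5.1), SOPs must cover use of the vaccine (section 7.3.2), and monitors check dosage (section 7.3.3). A systematic double dose would have to pass all of these.

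Much of this stands. The intended 2 mg is clear, the consequences depend on literal use of the note, and misdosing is not shown. The release range applies to every arm alike and does not explain the discrepancy.

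It does not clear the text. The protocol states a volume, and for one arm that volume gives the wrong dose. Section 7.3.2 binds sites to the protocol as well as to the SOPs, and section 7.3.3 has monitors verify dosage and administration against the protocol. A correct 0.5 ml draw departs from Note (1), and a 1 ml draw departs from Table 5, so a monitor has no consistent standard to check against.

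On placebo, it is fair to say that the equal-volume rule governs, and that 1 ml read as a total matches a correct low-dose preparation. But that rule points to a low-dose volume which the note itself gets wrong. The ambiguity is real but secondary, and unblinding is not shown.

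**Conclusion.** The protocol is wrong as written. Its one DNA preparation instruction gives 4.0 mg in an arm assigned 2 mg, a two-fold excess per vaccination and 12 mg against 6 mg per participant. The calculation rests only on the protocol's own strength, volume and composition, and nothing in the document supplies another volume for the low dose.

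The loss of the dose step, of the 2 mg safety data and of the dose contrast follows only if the note is applied literally to DNA-L+rTV. Instructions for use or SOPs not shown here may prevent that, but they would not correct the protocol. Because the conflict concerns the dose in the arm that opens the trial, it must be fixed before dosing. The placebo volume should be settled in the same edit.

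**What to change.** In section 2.4 and in Table 5, Note (1):

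- Limit 1 ml of each plasmid at 2.0 mg/ml to the 4 mg arms (DNA-H+rTV and DNA-only).
- For DNA-L+rTV, state 0.5 ml of each plasmid at 2.0 mg/ml, 1.0 ml in total.
- State the placebo volume per deltoid to match the low-dose arm: 0.5 ml per side, assuming the active volume is split equally between the arms.

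If the sponsor prefers the same injected volume at both dose levels, the low dose can be 1 ml of each plasmid diluted to 1.0 mg/ml, with 1 ml of placebo per side. That adds a dilution step which the protocol does not now contain, so the 0.5 ml draw is simpler.

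With the 0.5 ml draw the change is wording in two places, made before first dosing, with no extra participants or visits. Any instructions for use or SOPs that give volumes should be checked against the corrected text.

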**Table 7. Blood collection form (the vaccination week is week 0) Unit: ml**

| week                                    | -1 | 0   | 4   | 6   | 8   | 10  | 12  | 12.5 | 13 | 14  | 16  | 20  | 24  | 28  | 32  | 36  |
|-----------------------------------------|----|-----|-----|-----|-----|-----|-----|------|----|-----|-----|-----|-----|-----|-----|-----|
| Routine blood test               | 2E |     | 2E  |     | 2E  |     | 2E  |      | 2E | 2E  | 2E  | 2E  | 2E  | 2E  | 2E  | 2E  |
| Liver and kidney functions + CK  | 2  |     | 2   |     | 2   |     | 2   | 2    | 2  | 2   | 2   | 2   | 2   | 2   | 2   | 2   |
| CK-MB+cTnI                       | 3  |     | 3   |     | 3   |     | 3   | 3    | 3  | 3   | 3   | 3   | —   | —   | —   | 3   |
| Syphilis test                    | 2  |     |     |     |     |     |     |      |    |     |     |     |     |     |     | 2   |
| IgG, IgA, IgM                    | 2  |     |     |     |     |     | 2   |      |    |     |     |     |     |     |     | 2   |
| DNA/ANA antibody                 | 2  |     | 2   |     | 2   |     | 2   |      |    |     |     |     |     |     |     | 2   |
| HbsAg + HCV antibody             | 2  |     |     |     |     |     |     |      |    |     |     |     |     |     |     | 2   |
| HIV antibody                     |    |     | 2   |     | 2   |     | 2   |      |    | 2   | 2   | 2   | 2   | 2   | 2   |     |
| T-cell phenotype.                | 8E |     |     |     |     |     | 4E  |      |    |     |     |     |     |     |     |     |
| HIV nucleic acid test            |    |     | *   |     | *   |     | *   |      |    | *   | *   | *   | *   | *   | *   |     |
| HIV cellular responses (ELISPOT) |    | 14E | 14E | 14E | 14E | 14E | 14E |      |    | 14E | 14E | 14E | 14E | 14E | 14E | 16E |
| Vaccinia virus antibody          | 2E |     |     |     |     |     |     |      |    | 16E | 16E | 16E | 16E | 16E | 16E | 16E |

|                                              |           |            |            |            |            |            |            |           |           |           |           |           |           |           |           |           |
|----------------------------------------------|-----------|------------|------------|------------|------------|------------|------------|-----------|-----------|-----------|-----------|-----------|-----------|-----------|-----------|-----------|
| HIV antigen specific antibody (ELISA) |           | 16E | 16E | 16E | 16E | 16E | 16E |           |           |           |           |           |           |           |           |           |
| HIV cellular responses (ICS)          |           |            |            |            |            |            |            |           |           |           |           |           |           |           |           |           |
| HIV neutralizing antibody             |           |            |            |            |            |            |            |           |           |           |           |           |           |           |           |           |
| Cell cryopreservation                 |           |            |            |            |            |            |            |           |           |           |           |           |           |           |           |           |
| HLA typing                            |           |            |            |            |            |            |            |           |           |           |           |           |           |           |           |           |
| Vaccinia virus culture                |           |            |            |            |            |            |            | 7E | 7E | 7E | 7E |           |           |           |           |           |
| Total                                 | 25 | 30  | 41  | 30  | 41  | 30  | 47  | 12 | 14 | 46 | 46 | 39 | 36 | 36 | 36 | 47 |

